Therefore, the primary purpose of this study is to compare the effects of delivering an entirely virtual 6-month supervised MVPA group plus standard exercise counseling (PA + EC) versus a virtual supervised MVPA plus motivationally-enhanced behavioral counseling (PA + BC) group on MVPA in people LWBC. We hypothesize that the PA + BC group will increase MVPA compared to the PA + EC group at mid-intervention (T1; 3 months), post-intervention (T2; 6 months), 6-month follow-up (T3; 6 months post-intervention), and 1-year follow-up (T4; 1-year follow-up from post-intervention). Secondary outcomes include: (1) to determine the effects and cost-effectiveness of PA + EC versus PA + BC on secondary outcomes, including changes in reflective, regulatory, and reflexive processes from the M-PAC, physical function, QoL and costs; (2) to examine the regulatory and reflexive mediators of the 6-month intervention on MVPA; and (3) to examine moderators of treatment efficacy in the PA intervention. We will compare across various demographics (e.g., intersection of age, sex, gender, ethnicity, body mass index), fitness (e.g., baseline PA), and clinical subgroups (e.g., cancer type), as well as adherence and intervention completion across groups. This study will address gaps in the PA maintenance literature to demonstrate: (1) changes in absolute values across behavioral performance of people LWBC, (2) an increase in their magnitude of effect on PA over time; [26] and (3) sex and gender differences in PA maintenance.

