**Secondary outcomes**						
Quality of life (Functional Assessment of Cancer Therapy [FACT]-General, FACT-Fatigue, Fatigue subscale, EuroQol-5D)	20 min	X	X	X	X	X
Measures from the Multi-process Action Control (M-PAC) framework (affective attitudes, instrumental attitudes, injunctive norms, descriptive norms, and perceived control, behavioral regulation for physical activity, physical activity habits, exercise identity)	15 min	X	X	X	X	X
Physical function (i.e., 30-second chair stand, 6-minute walk test)	30 min	X	X	X	X	X
Demographic, medical and health history questionnaire	10 min	X				
Health economics (Health Services Utilization Inventory, iMTA Productivity Cost Questionnaire, Incremental Cost of Intervention)	20 min	X	X	X	X	X
Participant satisfaction questionnaire	5 min			X		
Adherence and compliance (Physical activity log)	5 min	assessed throughout intervention				
Fidelity and quality control (Fidelity checklists)	5 min	assessed throughout intervention				
Adverse events (Adverse events log)	5 min	assessed throughout intervention				

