10 Group	*Target M-PAC construct: Regulatory processes (coping planning*,* emotion regulation)* Discussing common psychologic, emotional, and environmental barriers to physical activity and strategies to overcome them	1.1 Goal setting (behavior) 1.2 Problem solving 1.4 Action planning 1.8 Behavioral contract 2.3 Self-monitoring of behavior 2.6 Biofeedback 7.1 Prompt/cues 10.7 Self-incentive 11.2 Reduce negative emotions 15.4 Self-talk	Stretching routine
12 1:1	*Target M-PAC construct: Regulatory processes (social support)* Discussion of social support and how to obtain support from significant others (i.e., spouse, friend, siblings)	3.2 Social support (practical) 12.1 Restructuring the physical environment 12.2 Restructuring the social environment	How to progress safely through a physical activity program
14 Group	*Target M-PAC construct: Reflexive processes (habit)* Identifying environmental cues to increase physical activity such as cues paired with time of the day, place, event, or other habits	7.1 Prompt/cues 7.5 Remove aversive stimulus 7.8 Associative learning 8.1 Behavioral practice 8.3 Habit formation	What to wear during physical activity
16 1:1	*Target M-PAC construct: Reflexive processes (habit)* Reinforcing a physical activity routine based on tagging physical activity to existing schedule and reminders strategies to reinforce the cues	7.1 Prompt/cues 7.5 Remove aversive stimulus 7.8 Associative learning 8.1 Behavioral practice 8.3 Habit formation	Importance of hydration
18 Group	*Target M-PAC construct: Reflexive processes (identity)* Building a physical activity identity by brainstorming and prioritizing various identities and where physical activity fits in	6.2 Social comparison 8.1 Behavioral practice 8.2 Behavioral substitution 12.5 Adding objects to the environment 13.2 Framing/reframing 13.3 Incompatible beliefs 13.4 Valued self-identity 13.5 Identity associated with changed behavior	Cross training
20 1:1	*Target M-PAC construct: Reflexive processes (identity)* Continue building a physical activity identity by prioritizing physical activity and finding personal meaning in participating in physical activity	6.2 Social comparison 8.1 Behavioral practice 8.2 Behavioral substitution 12.5 Adding objects to the environment 13.2 Framing/reframing 13.3 Incompatible beliefs 13.4 Valued self-identity 13.5 Identity associated with changed behavior	Feedback for progress to date

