#### Statistical analysis

A series of multilevel models using full information maximum likelihood to examine changes in the primary (i.e., MVPA) and secondary outcomes (i.e., reflective, regulatory, and reflexive processes from the M-PAC, physical function, QoL) will be conducted at the four time points. Multilevel modelling allows for simultaneous assessments of within person variations at each time measurement (level 1), which will be nested within study group (level 2). Finally, study group will be nested within study site (level 3). Although our primary time point of T2 will confirm the adherence reported post-intervention, inclusion of the T3 and T4 assessments allows us to determine if adherence is maintained. Fixed effects included in models will be time (i.e., baseline, T1, T2, T3, and T4), group (i.e., PA + BC intervention and PA + EC attention control), and interaction. All models will be estimated while adjusting for covariates (e.g., baseline PA, age, sex, treatment and cancer type). We will use the same analytical approach to assess differences across subgroups (e.g., sex, gender, drop-outs) by modeling the changes over time. Differences between men and women will be analyzed by adding a gender indicator variable to each of the models. The gender covariate will be crossed with the model’s independent variable so their interaction will be in the model. An intention-to-treat analysis will be used. For missing data at post-intervention or follow-up, all available data will be included under the missing-at-random assumption of the mixed-model analysis. Additionally, sensitivity analyses will be conducted to evaluate the robustness of our findings under alternative missing data assumptions, such as not-missing-at-random. The PROCESS macro for SPSS [77] will be used to examine mediation effects of the reflective, regulatory, and reflexive processes between groups (PA + BC group; PA + EC group) and MVPA and indirect effects across the path model. Cost and QALY differences between groups will be calculated using ordinary least squares regression analyses. Incremental cost-effectiveness ratios (ICER) will be calculated by dividing the adjusted incremental costs by incremental effects. ICER uncertainty will be measured by bootstrapping using at least 5000 replications.

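### Mediation is assigned to a complete-case tool, outside the all-available-data rule, and no mediator and outcome waves are set, which matters for habit and identity

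*Protocol article*

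**What the plan says.** The last paragraph of the Background makes mediation a numbered secondary aim: "to examine the regulatory and reflexive mediators of the 6-month intervention on MVPA". The Statistical analysis section names the tool, "The PROCESS macro for SPSS [77] will be used to examine mediation effects of the reflective, regulatory, and reflexive processes between groups", and continues "and MVPA and indirect effects across the path model". It does not say which visit supplies the mediator and which supplies MVPA, and it gives no missing-data rule for this analysis.

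For the primary and secondary outcomes the same section specifies "A series of multilevel models using full information maximum likelihood to examine changes in the primary" and the secondary outcomes. It adds that "all available data will be included under the missing-at-random assumption of the mixed-model analysis", and that "sensitivity analyses will be conducted to evaluate the robustness of our findings under alternative missing data assumptions".

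Table 3 dates the counselling content. The first habit session, in week 14, is described as "Identifying environmental cues to increase physical activity such as cues paired with time of the day, place, event, or other habits". Habit and identity fill weeks 14, 16, 18 and 20. Under Data collection, T1 is 3 months into the intervention, and all primary and secondary outcomes are measured at all five visits.

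The list of constructs varies. The aim names two classes of mediator, while the analysis paragraph adds the reflective class. Table 1 lists "injunctive norms, descriptive norms, and perceived control" where the Background and the Secondary outcomes section list perceived capability and opportunity.

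**The concern.** There are two separate problems.

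**Missing data.** The estimator is named in the text, so it is not simply left to a later document. PROCESS, run as supplied, drops any participant who lacks the mediator or the outcome. In a trial of behavioural maintenance, people who become less active may well be the ones who stop returning accelerometers. If so, the two paths of the indirect effect are estimated in a selected group. The mixed model guards against this for the other outcomes, but nothing stated guards against it here.

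**Temporal order.** The Background presents habit and identity as the constructs that may explain maintenance. It also describes them as developing out of repeated successful behaviour. On that account activity produces habit as well as the reverse, so a mediator and an outcome from the same visit cannot show direction. A mediator measured before the habit and identity sessions cannot carry their effect. What is at stake is the interpretation of the mechanism aim, not the group comparison of MVPA.

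**Working it through.** **1. Sample left for a complete-case analysis.** Inputs from the Sample size section: 196 needed, 20% attrition, target 236.

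- The plan's own figure: 196 × 1.20 = 235.2, which gives 236 in two equal arms. Reproduced.
- Complete cases: 236 × (1 − 0.20) = 188.8, about 189. This assumes that the 20% applies at the visits used. Isolated missed visits would lower it.
- The plan states no sample size or power for mediation to compare this with.

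**2. Possible bias.** The documents give no mediation paths and no drop-out model, so every figure here is an illustration under assumed values.

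- *Run A.* n = 236, 2,000 replicates, standard normal errors e:
  - T1 MVPA = 0.3·group + 0.5·U + 0.85·e, with U a standard normal person effect
  - mediator = 0.4·group + 0.3·(T1 MVPA) + 0.9·e
  - later MVPA = 0.3·mediator + 0.4·(T1 MVPA) + 0.8·e
  - logit of drop-out = −1.4 − g·(T1 MVPA)

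| g | Mean retained | Mean listwise indirect effect | Attenuation against g = 0 |
|---|---|---|---|
| 0 | 189.3 | 0.2089 | reference |
| 0.5 | 189.7 | 0.2071 | 0.0018 / 0.2089 = 0.9% |
| 1.0 | 185.7 | 0.1983 | 0.0106 / 0.2089 = 5.1% |

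The Monte Carlo error of each mean is about 0.07/√2000 = 0.0016, so the 0.9% cannot be told from zero.

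- *Run B.* n = 236, 6,000 replicates, 18% drop-out driven by low T1 MVPA and more weakly so in PA + BC, paths near 0.4 and 0.5. Indirect effect 0.195 with no drop-out and 0.173 listwise: 0.022/0.195 = 11%.
- *Further runs with other assumed values.* About 0% when drop-out is unrelated to T1 MVPA; 3% to 7% with moderate dependence and 16% with strong dependence; 6% with equal dependence in both arms; 11% to 16% when the dependence is weaker in PA + BC.

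Overall range: about 0% to 16%. In the check that fitted both methods under the same drop-out, full information maximum likelihood removed the bias.

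**3. Precision.** In run B the standard deviation of the estimate rose from 0.062 to 0.067, a ratio of 1.08. Losing 18% of a sample at random would alone give 1/√0.82 = 1.10. In the head-to-head check the standard errors of full information maximum likelihood and listwise deletion were nearly equal (0.094 and 0.093). The extra standard error is therefore mostly the price of drop-out, and changing the method would not recover it.

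**4. Timing.** T1 at 3 months is 3 × 30.4375/7 = week 13.0.

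| Process | Weeks in Table 3 | Delivered by T1 |
|---|---|---|
| Reflective | 2 | 1 of 1 |
| Regulatory | 4, 6, 8, 10, 12 | 5 of 5 |
| Reflexive | 14, 16, 18, 20 | 0 of 4 |

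Possible pairings for each process:

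- Reflective or regulatory at T1 with MVPA at T2: correctly ordered.
- Reflexive at T1 with MVPA at T2: the mediator precedes all of its own content.
- Reflexive at T2 with MVPA at T2: same visit, so direction is not identified.
- Reflexive at T2 with MVPA at T3 or T4: ordered, with a lag of 6 or 12 months, using data already scheduled.

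**The case against.** The strongest reply is that the plan commits to less than a reader might infer.

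- **Waves.** A reader might conclude that the mediation analysis is largely concurrent or mistimed. The text does not support this: it names no waves, the five-visit schedule permits an ordered analysis of every process, and PROCESS itself could run T2 mediators against T3 or T4 MVPA. An article may leave the choice of waves to a fuller plan. Placing habit and identity late also fits the theory. All of this stands, and it confines the timing point to reflexive processes analysed with MVPA at T2, the stated primary time point.
- **Missing data.** A reader might see a contradiction with the promise to use all available data. There is none, because that promise is worded for the mixed model. Complete-case regression is a property of the named tool, not something the article states. Imputation beforehand is not excluded, and the promised sensitivity analyses refer to the findings in general. This stands too, but it leaves mediation with no stated protection in its main analysis.
- **Covariates.** The section adjusts all models for covariates such as baseline PA. If that covers mediation, drop-out that depends only on those covariates does little harm to complete-case regressions. The bias in question needs drop-out that depends on activity after randomisation, such as MVPA at T1.
- **Size.** Run B compares listwise deletion with no drop-out in one assumed scenario, and its shift of 0.022 is about a third of one sampling standard deviation (0.022/0.062 = 0.35). It should be read only as part of the range, and its precision loss should not be credited to the remedy.
- **Mediator list.** The three classes in the analysis include the two in the aim, so the aim is still served. The differing construct labels are a wording discrepancy that supports neither main point.

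**Conclusion.** The concern holds in limited form, as a cheap improvement to a secondary aim. Followed as written and with the tool's defaults, the mediation analysis would use about 189 of 236 participants. It would rest on a stronger missing-data assumption than the analyses beside it. The resulting bias may be nil or may reach roughly 16% attenuation; the documents cannot say which, because it depends on assumed paths and on whether drop-out follows post-randomisation MVPA. No material gain in precision should be expected from changing the method.

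The timing point is exact but conditional. None of the four reflexive sessions precedes T1, so neither T1-to-T2 nor T2-to-T2 can test habit and identity as mechanisms. That does not make the planned mediation concurrent as a whole: reflective and regulatory content is complete by T1, and no waves have been fixed. The primary MVPA comparison is unaffected.

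**What to change.** 1. Estimate mediation with a longitudinal path model fitted by full information maximum likelihood. Alternatively, keep PROCESS and run it after multiple imputation. In either case include earlier MVPA and earlier mediator values in the model, and use bootstrap intervals for the indirect effects.
2. State the waves: reflexive mediators at T2 against MVPA at T3 and T4; reflective and regulatory mediators at T1 against MVPA at T2 or later. Pairing with later visits makes step 1 more important, since more outcomes will be missing there.
3. Use one list of mediators and construct names in the Background aims, Table 1, the Secondary outcomes section and the Statistical analysis section.

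Cost: slightly more analysis work, and either different software or an imputation step. No new data are needed, because mediators and MVPA are already scheduled at all five visits.

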#### Monitoring

All personnel will be trained at the University of Toronto site to ensure quality control and fidelity (e.g., manual of operations, provider training [3 × 6-hour sessions], weekly conference calls with sites, intervention delivery checklists) using guidelines recommended by the National Institutes of Health (NIH) Behavior Change Consortium [78]. This includes best practice recommendations to address treatment fidelity across five domains: Study Design (e.g., user-friend scripted counseling sessions), Provider Training (e.g., role plays for skill acquisition), Treatment Delivery (e.g., ensure adherence to protocol via checklists), Treatment Receipt (e.g., assess patient’s confidence to apply skills learned), and Treatment Enactment (e.g., self-report engaging in physical activity). QEPs will undergo role plays with a scoring guide to ensure standardization.

A data audit will take place at least once per year to ensure forms are being completely accurately and timely. Depending on the pace of recruitment, these data audits may take place more frequently. For safety monitoring, all adverse events will be classified as either an adverse (AE) or a serious adverse event (SAE). These events may occur during screening and baseline data collection, or they may occur during the administration of the intervention. An adverse event may or may not be related to the data collection or intervention procedures. When an adverse event is identified, study personnel identifying the adverse event will report it to the research s and the Principal Investigator. The research co-ordinator will then contact the participant and an electronic Adverse Event Report Form will be submitted to the research ethics board will be completed within 7 days of the event and within 48 h for serious adverse events. Decisions to discontinue or modify the intervention for a participant will be on a case-by-case basis by the research team.

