### Study design

This study is a two-armed, multi-site RCT, to examine the effects of PA + EC versus PA + BC on MVPA in people LWBC. A 6-month follow-up (T3) and 1-year follow-up (T4; 1-year follow-up from post-intervention) will take place after the intervention to address maintenance. The study flow is outlined in Fig. 1 and the study measurements, outcomes, and schedule are summarized in Table 1.

**Table 1 Tab1:** Outcome measures at each time point with time required for completion

Domain/Measure	Time Required for Completion	Baseline (month 0;T0)	Mid-point (month 3; T1)	Post-intervention (month 6; T2)	6-month follow-up (month 12; T3)	1-year follow-up (month 18; T4)
Eligibility		X				
Informed consent		X				
Group allocation (after completion of baseline, T0)		X				

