*Intervention Group - Physical Activity Group + Behavioral Counseling Group (PA + BC)-*The PA + BC group will receive a behavioral counseling support session with a QEP every two weeks during the intervention period (12 total). The support sessions will be 30–45 min and delivered via Zoom each week in either group or 1:1 format depending on the topic. The videoconference calls will incorporate tailored behavior change content from the M-PAC framework (Table 3; Fig. 2). Of the 12 video-conferencing calls, one session will target reflective processes (instrumental/affective attitudes), five sessions will target behavioral regulation (action planning, coping planning, social support, goal setting, emotion regulation), and four sessions will target reflexive processing (identity, habit). The remaining two sessions are “booster sessions” to revisit topics discussed. The importance of sustaining PA for clinical outcomes (e.g., fatigue) and PA logs will be stressed. At the end of the 6-month intervention, an individualized PA prescription will be provided based on their fitness level (adjusted throughout) to continue achieving the PA goal for the 6-month and 1-year follow-up.

*Attention Control Group ** Physical Activity Program + Exercise Counseling Group (PA + EC)-*The PA + EC group will receive the same frequency of group-based and 1:1 counseling support sessions via Zoom as PA + BC participants. However, the focus will be on PA training principles for proper PA technique, how to monitor intensity, and progress PA safely to achieve the PA guidelines. The support sessions will be 30–45 min and delivered via Zoom each week in either group or 1:1 format depending on the topic (Table 3; Fig. 2).

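### The stated adverse-event window leaves out follow-up months 6 to 18, although physical testing continues in both arms at months 12 and 18

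*Protocol article*

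**What the plan says.** Two places in the protocol article set out when adverse events are expected or collected.

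- **Monitoring.** The text names two periods: "These events may occur during screening and baseline data collection, or they may occur during the administration of the intervention". It then accepts that study assessments can themselves be a source of harm: "An adverse event may or may not be related to the data collection or intervention procedures".
- **Table 1.** The row "Adverse events (Adverse events log") carries no mark at individual visits. It has one entry, "assessed throughout intervention", and a completion time of 5 minutes.

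The intervention ends at "Post-intervention (month 6; T2") and follow-up ends at "1-year follow-up (month 18; T4").

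Two study activities continue beyond month 6. The Table 1 row "Physical function (i.e., 30-second chair stand, 6-minute walk test") is marked at all five time points, T3 and T4 included, and the Secondary outcomes section says that these tests are done remotely. In Study groups, the PA + BC paragraph says that when the intervention ends "an individualized PA prescription will be provided based on their fitness level (adjusted throughout"), and that it serves the PA goal over both follow-ups. The PA + EC paragraph has no matching sentence.

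**The concern.** The trial is about whether exercise is maintained once supervision ends. Under Study design, the T3 and T4 visits exist to address maintenance, and the Background hypothesises higher MVPA in PA + BC at both. Harm data should cover the same period as the benefit being claimed. As the window is worded, they do not.

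The plan's own logic points the other way. Monitoring recognises events linked to data collection and explicitly includes the baseline assessments. The same physical tests at months 12 and 18 fall outside both statements of the window. The exclusion criteria also treat unsupervised as well as supervised activity as a setting in which risk matters.

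If PA + BC keeps its participants more active in months 6 to 18, a difference in injuries or falls over those months could not be estimated from systematically collected data. The trial could report a sustained benefit with no comparable statement on harm.

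**Working it through.** The plan gives no figure on this point, so there is nothing of its own to reproduce. The check sets the statements side by side and then sizes the gap.

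**Coverage by period**

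| Period or visit | Monitoring text | Table 1 log | Study activity |
|---|---|---|---|
| Screening, baseline (T0) | named | not named | chair stand, 6-minute walk |
| Intervention, months 0–6 (T1, T2) | named | named | supervised and home sessions; tests at T1 and T2 |
| Months 6–12 (T3) | not named | not named | tests in both arms; prescription in PA + BC |
| Months 12–18 (T4) | not named | not named | tests in both arms; prescription in PA + BC |

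Table 1 marks T3 and T4 for the primary outcome, quality of life, the M-PAC measures, physical function and health economics. It therefore shows follow-up collection where that is intended. The adverse-event row shares its timing entry with the adherence log and the fidelity checklists, both of which belong to delivery of the intervention.

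**Size of the gap**

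Inputs: intervention ends at month 6 and follow-up at month 18 (Table 1); 236 participants, 118 per arm, expected attrition 20% (Sample size).

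1. Share of planned time outside the window: (18 − 6) / 18 = 12 / 18 = 0.667, or 67%.
2. Person-months with full follow-up: 236 × 12 = 2,832 outside, of 236 × 18 = 4,248 in total.
3. Range for attrition. Assume, as an extreme case, that all 20% leave at month 6: 0.8 × 236 × 12 ≈ 2,266 outside. The total is 236 × 6 + 2,266 = 1,416 + 2,266 = 3,682. The share is 2,266 / 3,682 ≈ 62%.
4. Range for the length of the intervention. Taken as exactly 24 weeks, it lasts 24 / 52 × 12 ≈ 5.54 months, and the share is 1 − 5.54 / 18 ≈ 69%.
5. Physical-function assessments outside both statements: T3 and T4, so 2 of 5.
6. Follow-up time documented as under a study prescription, PA + BC only: 118 × 12 = 1,416 of 4,248 person-months, or 33%.

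The 67% is therefore calendar follow-up time in both arms. Only half of it (1,416 of 2,832) is documented as time under a study prescription.

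**The case against.** The strongest reply is that the documents do not say that collection stops. The Monitoring sentence describes when events might arise, the section promises to classify all adverse events, and the instruction that staff report an event they identify has no time limit. A fall that an assessor learns of at the T3 walk test would be reportable. This stands. A reader might infer that follow-up events would be neither logged nor reported, and the text does not support that. But classifying and reporting an event presuppose that someone has found it, and no instrument is scheduled to look for events after month 6, when the classes and counseling have ended.

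A second reply is that this is a condensed article, and that the fuller protocol or the manual of operations may set the follow-up schedule. That would decide the matter if the article were silent. It is not: it states a window in two places, and neither extends to follow-up.

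Other tempting readings go too far:

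- *All participants exercise under a study prescription to month 18.* The sentence appears for PA + BC only, and the unsupervised sessions prescribed to both arms fall in weeks 13 to 24, inside the intervention.
- *Any extra exercise from PA + BC falls outside the window.* Higher MVPA is also hypothesised at T1 and T2, and T2 is the primary time point. Both lie inside the window.
- *Table 1 and Monitoring conflict on baseline.* Monitoring covers baseline expressly, and the table entry is one text string in place of visit marks. This is loose wording that should be aligned, no more.

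Finally, the Health Services Utilization Inventory is completed at T3 and T4, so events leading to health-service use would leave a trace. It is a cost measure, however. Nothing routes it to adverse-event reporting, and events without service use would not appear in it.

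**Conclusion.** The point holds in a limited form. The stated adverse-event window does not include months 6 to 18, and no systematic ascertainment is scheduled there. That is 67% of planned time per participant (62% to 69% under the alternatives shown), and 2 of the 5 physical-function assessments in each arm. It rests on reading the Table 1 entry and the two periods named in Monitoring as the schedule for collection. A fuller document could show otherwise, but the article would then need correcting to match it.

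The primary comparison at T2 is unaffected, because efficacy and harm data cover the same period up to that point. What suffers is any claim at T3 or T4, which would have no matching harm data by arm. The documents do not show that events would go unreported, nor that harm in either arm is likely. This should be changed, and it is easy to change.

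**What to change.** Reconcile Table 1, Study groups and Monitoring on the adverse-event window:

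1. Extend the Table 1 adverse-event row through T4, and align its start with the baseline wording in Monitoring.
2. Name the follow-up period and the T3 and T4 assessments in the Monitoring sentence.
3. At T3 and T4, have the blinded assessors ask the same standard adverse-event question in both arms, covering the time since the last visit. Asking it after the physical tests also captures an event during the test.
4. Report intervention-period and follow-up events separately, by arm.
5. State in Study groups whether the prescription at the end of the intervention is given in one arm or both, so that follow-up harm data can be read against the exposure.

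The cost is a wording amendment and about 5 minutes per participant (the time Table 1 allots to the log) at two visits already scheduled. The drawback is recall over 6-month intervals, which will under-count minor events. The under-count may not be equal by arm: Table 3 gives PA + EC, but not PA + BC, a session on signs and symptoms for stopping activity, which could affect recognition and recall. Follow-up counts should be reported with that caution.
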